### Data collection

Participants' baseline data will be collected three days before discharge, and a questionnaire regarding demographics will be completed. Data collection will be conducted at 3 and 6 months after discharge. Patients will attend clinical appointments in the study hospital or designated community hospitals to complete clinical and laboratory assessments. Research assistants will upload the results to the diabetes management platform for secure collection. The research assistant will collect the questionnaires face-to-face during the outpatient visit. The patients' blood glucose data and hypoglycemia events will be supervised and consulted by CNs through the app or telephone. Readmission will be determined by referring to the participant's medical history in the general hospital. All data will be double-entered and checked for consistency. The study flowchart and participant data collection are depicted in Fig. 1 and Table 1.

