### Statistical analysis

Data will be imported into SPSS 23.0 for further statistical analysis. Descriptive statistics, including the mean, standard deviation, and frequency, will summarize all participants' various factors. In order to determine whether the data met the planned statistical analysis hypothesis, the data were examined for distribution and collinearity before the analysis. The analysis will be based on an intention-to-treat (ITT), meaning that all eligible patient information was included in the analysis regardless of whether the intervention was completed. In the primary analysis, Student's t-tests or Mann–Whitney U tests will compare the differences in demographic and diabetes-related information in the two study groups at baseline and endpoint for continuous data or χ2 tests for proportions. The differential changes in repeated measurement data between groups will be assessed by repeated-measures ANOVA and the interaction effect (group × time) across three time points (baseline, three months, six months), aiming to evaluate the impact of the intervention over time on the primary study outcomes. The ITT analyses will also be used to impute missing study data. The analysis of secondary outcomes will be compared similarly to the primary analysis, except for the results of HbA_1c_ levels, where the remaining metrics will not be considered for repeated measurements based on the fact that they were measured ≤ 2 times. A p-value of less than 0.5 will be considered statistically significant.

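### Being measured at most twice is no reason to leave baseline out of the secondary-outcome comparisons; ANCOVA would gain precision at almost no cost

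*Protocol article*

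**What the plan says.** The Statistical analysis section of the protocol article names two between-group methods. The first is a t-test, Mann–Whitney U test or χ2 test, applied "in the two study groups at baseline and endpoint for continuous data or χ2 tests for proportions". The second is "repeated-measures ANOVA and the interaction effect (group × time) across three time points (baseline, three months, six months"), intended for the primary outcome.

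Secondary outcomes are to be handled like the primary, with one exception: apart from HbA1c, "the remaining metrics will not be considered for repeated measurements based on the fact that they were measured ≤ 2 times". Once the second method is removed, only the first is left. No change score and no baseline-adjusted model is named for the secondary outcomes.

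On timing, the Data collection section says "Participants' baseline data will be collected three days before discharge" and then "Data collection will be conducted at 3 and 6 months after discharge". Patients attend these appointments "to complete clinical and laboratory assessments", and "The research assistant will collect the questionnaires face-to-face during the outpatient visit". For the schedule it refers to a figure and a table: "The study flowchart and participant data collection are depicted in Fig. 1 and Table 1".

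**The concern.** The number of measurements is used to settle a question it does not settle. Having at most two values is a reason not to fit a three-time-point ANOVA. It is no reason to keep the baseline value out of the effect estimate, because a baseline and one follow-up value are all that ANCOVA needs.

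The secondary objectives are framed as improvement in lipids, blood pressure, BMI, self-management and knowledge. Under the stated plan, each of these would be judged by one test at baseline and another at the endpoint, with nothing linking the two. If the arms differ by chance at baseline, part of that difference carries through to the endpoint and the stated test cannot remove it. If the baseline value predicts the endpoint, variance that could be explained stays in the error term. In a trial of this size both effects are large enough to matter for how the secondary results are read.

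**Working it through.** **The plan's own figure.** The Sample size section gives a difference of 0.5, SD 1, power 0.80 and two-sided alpha 0.05. Then n per arm = 2 × (1.960 + 0.842)² × 1² / 0.5² = 62.8, rounded up to 63, or 126 in total. This matches the stated 126. The plan enrols 69 per arm and allows 10% attrition: 69 × 0.90 = 62.1, so about 62 per arm are analysed. The sizing is for HbA1c only; no figure is given for any secondary outcome.

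**Assumed inputs.** The documents give no baseline-to-endpoint correlation r and no effect size for the secondary outcomes. I take r from 0.3 to 0.7 and carry over a standardised effect of 0.5 SD from the HbA1c calculation. Both are illustrative.

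**Precision.** With equal SD at the two times, the variance of the treatment contrast relative to the endpoint-only comparison is:

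- endpoint only: 1
- change score: 2(1 − r)
- ANCOVA: 1 − r²

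ANCOVA power is approximated by a two-sample t-test with effect 0.5 / √(1 − r²), 62 per arm and two-sided alpha 0.05:

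| r | 1 − r² | Effective d | Power |
|---|---|---|---|
| no adjustment | 1.00 | 0.500 | 0.79 |
| 0.3 | 0.91 | 0.524 | 0.83 |
| 0.5 | 0.75 | 0.577 | 0.89 |
| 0.6 | 0.64 | 0.625 | 0.93 |
| 0.7 | 0.51 | 0.700 | 0.97 |

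Seen the other way, leaving baseline out multiplies the variance by 1/(1 − r²): 1.10 at r = 0.3, 1.33 at r = 0.5 and 1.96 at r = 0.7.

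A plain change score is not an equivalent remedy. Its factor is 1.4 at r = 0.3 (worse than endpoint only), 1.0 at r = 0.5 (no gain) and 0.6 at r = 0.7 (still above ANCOVA's 0.51).

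**Chance imbalance.** The standard error of a baseline mean difference is √(2/62) = 0.18 SD. A difference of more than 0.2 SD in either direction is 0.2/0.18 = 1.11 standard errors, which has probability of about 0.27 for any one measure. The unadjusted endpoint contrast is then shifted by r times the imbalance, for example 0.5 × 0.2 = 0.10 SD.

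**Which outcomes.** Blood pressure, TC, TG, LDL, HDL, BMI, SDSCA, DSQL and DKT are continuous measures that can have a baseline value. Satisfaction with transitional care and readmission have no natural pre-discharge value, so the point does not reach them.

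**Visit count.** Read on its own, the Data collection section suggests three occasions (baseline, 3 and 6 months) and restricts no outcome to fewer. The Statistical analysis section says at most two. But Data collection does not assign individual outcomes to visits, and it refers to the outpatient visit for questionnaires in the singular. The schedule it points to, Table 1, cannot be seen in the copy reviewed.

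**The case against.** Four points can be made for the plan.

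First, in a 1:1 randomised trial an unadjusted endpoint comparison is unbiased on average and keeps its type I error, so the loss is one of efficiency and not of validity. This stands, and the point is framed accordingly.

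Second, baseline is compared between the groups, so it is not thrown away. This also stands: baseline is left out of the treatment contrast, which is narrower than being discarded.

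Third, this is a condensed article, and covariate adjustment is often left to a statistical analysis plan. That carries less weight here, because the article states a method for these outcomes and gives a reason for it. The reason is what fails.

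Fourth, the size is illustrative: the effect is borrowed from HbA1c, and at r = 0.3 the gain is only from 0.79 to 0.83. This is fair, and it is why the low end is shown.

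A reader might also infer that the count of at most two measurements flatly contradicts a three-visit schedule. The documents do not support that. A trial can hold three visits, measure HbA1c at all of them and measure lipids or questionnaires at only two, and Table 1 may say exactly this.

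**Conclusion.** The concern holds in limited form. For continuous secondary outcomes with a baseline value, the stated plan leaves baseline out of the treatment contrast, and the number of measurements does not justify that. The cost is lost precision and uncorrected chance imbalance, with no bias on average. With 62 per arm and a 0.5 SD effect, baseline adjustment would raise power from 0.79 to between about 0.83 (r = 0.3) and 0.97 (r = 0.7). Both r and the effect size are assumptions; the direction of the gain does not depend on them, apart from one degree of freedom when r is close to zero. The stated sample size and the HbA1c analysis are unaffected.

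The visit count is a matter to reconcile and does not bear on this conclusion: baseline should be used whether there are two measurements or three.

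**What to change.** - For each continuous secondary outcome with a baseline value (blood pressure, each lipid, BMI, SDSCA, DSQL, DKT), estimate the treatment effect by ANCOVA on the 6-month value with its own baseline as covariate, and report the adjusted difference with a 95% confidence interval. Keep the baseline comparison as description only.
- Leave satisfaction and readmission to methods that need no baseline.
- Check the count of at most two measurements against the Data collection section and Table 1, and make the three agree. If a 3-month value is collected for any of these outcomes, it can be included in a baseline-adjusted longitudinal model. That model would have to be specified, because the plan currently names only repeated-measures ANOVA, and only for HbA1c.

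The cost is a change of wording in the analysis section. The ANCOVA needs only the baseline and 6-month values, so no extra visits, measurements or participants are required.

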### Study design

This study is a multicenter pragmatic RCT with a 6-month follow-up period performed at a large general hospital and in 8 communities in Shanghai, China. The study will be conducted with a transitional care team that includes clinical nurses certified in diabetes care, physicians, endocrinologists, community nurses (CNs), general practitioners (GPs), pharmacists and administrative support staff to begin mHealth-based integrated hospital-community-home (i-HCH) transitional care to facilitate the glycemic control of discharged patients with T2DM and guide their self-management skills. Patients who meet the eligibility criteria will be included and randomized to receive the i-HCH transitional care or usual transitional care intervention. The allocation ratio will be 1:1. Due to the characteristics of the study, trial team members and participants will not be blinded, while the data collectors and statistical analysis assistants will be blinded.

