### Sample size

Our sample size estimation was performed using R Studio software based on HbA_1c_. A total of 126 participants from an endocrinologist in the general hospital are required to detect a mean difference in HbA_1c_ of 0.5% over six months between the intervention and control groups with a standard deviation of 1 to achieve 0.8 power and a two-sided alpha of 0.05. Allowing for a 10% attrition rate, the total participant number should be 138, or with 69 participants in each group.

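### The analysis section sets significance at p < 0.5, contradicting the two-sided alpha of 0.05 behind the sample size; applied as written it gives a 50% false-positive rate per test

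*Protocol article*

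**What the plan says.** The last sentence of the protocol article's Statistical analysis section reads: "A p-value of less than 0.5 will be considered statistically significant". It carries no qualification. It follows the description of the baseline and endpoint comparisons, the repeated-measures ANOVA with its group-by-time interaction for HbA1c, and the analysis of the secondary outcomes, so it applies to all of them. The section gives no other threshold.

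The Sample size section, immediately before it, describes a trial "required to detect a mean difference in HbA_1c_ of 0.5% over six months between the intervention and control groups", "with a standard deviation of 1", and sized "to achieve 0.8 power and a two-sided alpha of 0.05". The resulting number is "A total of 126 participants" before attrition.

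**The concern.** The two sections give different significance levels for the same trial, 0.5 and 0.05, and both cannot hold. The alpha in a sample size calculation is a planning input. The sentence in the analysis section is the one that fixes how results will be judged, and that is where the implausible value stands.

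A published protocol is the reference for what was pre-specified. Read literally, this one allows results compatible with chance to be reported as significant by the pre-specified rule. If every null hypothesis were true, half of all comparisons would be called positive.

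**Working it through.** **Inputs (Sample size and Study design sections).** Difference δ = 0.5 HbA1c percentage points; SD σ = 1; power 0.80; two-sided α = 0.05; 1:1 allocation; 126 evaluable (63 per group); 138 enrolled (69 per group) after a 10% attrition allowance. **From the Statistical analysis section:** threshold p < 0.5.

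**Step 1: reproduce the plan's own figure.** With the normal approximation,

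n per group = 2σ²(z₁₋α/₂ + z₀.₈₀)² / δ²

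| Significance level | z for α | Calculation | n per group | Total |
|---|---|---|---|---|
| Two-sided 0.05 | 1.960 | 2 × (1.960 + 0.842)² / 0.25 = 62.8 | 63 | 126 |
| One-sided 0.05 | 1.645 | 2 × (1.645 + 0.842)² / 0.25 = 49.5 | 50 | 100 |
| Two-sided 0.5 | 0.674 | 2 × (0.674 + 0.842)² / 0.25 = 18.4 | 19 | 38 |

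Two-sided 0.05 matches the stated 126 exactly. The t-distribution version gives 64 per group, 128 in total, which is close. Neither a one-sided 0.05 nor a threshold of 0.5 gives anything near 126. The trial was therefore designed at two-sided 0.05.

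**Step 2: error rate under each rule.** A valid test at threshold α rejects a true null with probability α, so 50% at 0.5 and 5% at 0.05. A simulation of 40,000 null trials with 63 per group, analysed by t-test, gave 49.8% and 5.1%.

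**Step 3: smallest HbA1c difference that would be called significant.** For a two-group comparison of means this is z₁₋α/₂ × σ√(2/n). With n = 63, √(2/63) = 0.178.

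- At 0.5: 0.674 × 0.178 = 0.12 percentage points.
- At 0.05: 1.960 × 0.178 = 0.35 percentage points.

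With 62 per group (69 less 10%, that is 62.1) and the t-distribution on 122 degrees of freedom, the figures are 0.1215 and 0.3555. The choice makes no practical difference. A difference of 0.12 is about a quarter of the 0.5 the trial is designed to detect (0.12 / 0.5 = 0.24).

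**Step 4: nominal power.** At 63 per group, power for the 0.5-point difference is 80.1% at two-sided 0.05, as planned. It would be 98.3% at 0.5, bought entirely by the inflated type I error.

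**Step 5: secondary outcomes.** Count systolic and diastolic pressure (2), four lipids (4), BMI (1), self-management, quality of life and knowledge scores (3), satisfaction (1) and readmission (1): 12 measures. If all 12 nulls were true, the expected number of false positives is 12 × 0.5 = 6, against 12 × 0.05 = 0.6.

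**The case against.** The strongest reply is that this is a misprint and nothing more. The sample size can be reproduced only at 0.05, so an attentive reader can recover the intended level. No calculation in the protocol is wrong on this point, and readers given exact p-values can apply 0.05 for themselves. On that view the 50% error rate describes a literal reading that nobody would follow.

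Most of that is fair. A misprint is by far the likeliest explanation, the problem is an inconsistency between two sections rather than a faulty calculation, and the 50% figure is conditional on using the sentence as it stands. None of this removes the need to correct it. The sentence is the only decision rule in the analysis section, the article does not correct it anywhere, and a pre-specified criterion should not have to be inferred from a different section.

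The sizes given above are also partly illustrative. The smallest significant differences belong to a two-group comparison of means, not to the repeated-measures interaction test that the protocol also specifies for HbA1c. The count of 12 secondary measures is a reading of the outcome list, which does not say whether blood pressure components or questionnaire subscales are tested separately. These caveats change the illustrations but not the tenfold difference in error rate.

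**Conclusion.** The threshold is wrong as written and must be corrected. It contradicts the trial's own design level, and the stated 126 participants show that 0.05, two-sided, is the level the trial was built on. If the sentence were followed, type I error per test would be 50% instead of 5%; this needs only that the tests are valid. The figures of about 0.12 against 0.35 HbA1c points assume a two-group comparison with SD 1 and 63 per group. The figures of 6 against 0.6 false positives assume 12 secondary tests with every null true. The sample size calculation at two-sided 0.05 stands and needs no change on this account.

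**What to change.** In the final sentence of the Statistical analysis section, replace 0.5 with 0.05 and state that tests are two-sided, so that it agrees with the Sample size section. Publish this as a correction to the article, and confirm that the full protocol and any SAP already use two-sided 0.05. The cost is a one-line text correction; sample size, data collection and trial conduct stay as they are.

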## Discussion

As core members of primary care teams, CNs are becoming increasingly important in addressing the epidemic of chronic disease. CNs potentially have more excellent opportunities and the ability to provide continuing care than traditional clinical nurses, but lack professional training [8]. Communities have had insufficient resources to support such services on their own in China, and CNs have little capacity to meet certain patients' needs. Patients are usually seen in general hospitals, leading to overcrowding in hospitals, long waiting times, and overloading of transport and medical resources [37]. Community hospitals' strengths and services remain underused in chronic disease care. The local context has an important impact on the feasibility of forms of care [5]. Support for continuous and cooperative care with T2DM patients has not been achieved because of the lack of access to shared health information and work descriptions of different positions between local health care settings. In addition, patients' family members are extrinsic motivators to perform blood glucose management, and providing better family support and improving diabetes-related knowledge and attitudes will likely improve patients' health behaviors and outcomes [38, 39].

Specialist cooperation with primary care could reinforce glycemic control and prevent diabetes-related complications for T2DM patients. The i-HCH transitional care intervention was designed as a pragmatic RCT examining the feasibility of implementing continuing care in multiple settings via an app in the real-world setting of a hospital-community-home alliance. One of the key strengths of the study is refocusing on the cooperation and agreement between local hospitals and communities by designing a transitional care team workflow integration and emphasizing the complementary role of family members in disease management. The study addresses the discontinuity of information, contact and management in transitional care by clarifying team members' roles and work responsibilities and unifying network systems and devices. Ultimately, this study aims to optimize medical resource utilization to improve disease outcomes. The intervention has the potential to demonstrate significant improvements in diabetes-related biochemistry, self-management ability, quality of life and satisfaction of care for T2DM patients. If successful, it will positively impact T2DM patients, family members, health caregivers, and policymakers. This collaborative intervention program will continue to be applied in the hospital-community-home setting. If possible, we will analyze the cost-effectiveness of the intervention delivery and retention of app use at a later stage. Our study aims to verify the effectiveness of this program and directly contribute to constructing a research method for Chinese transitional care practice.

## Data Availability

Not applicable.

## Abbreviations

i-HCH: Integrated hospital-community-home
T2DM: Type 2 diabetes mellitus
mHealth: Mobile health
CNs: Community nurses
GPs: General practitioners
TC: Total cholesterol
TGs: Triglycerides
LDL: Low-density lipoprotein
HDL: High-density lipoprotein
BMI: Body mass index
